## Abstract

**Introduction::**

Uterine cervix tumors have an invasive nature, with the capacity to proliferate to surrounding organs such as the vagina, bladder, and rectum, as well as the capacity for dissemination and involvement of structures distant from its place of origin. According to the International Federation of Gynecology and Obstetrics, patients with stages IB I, IB I microscopic (small dimension <4 cm) are indicated for radiotherapy or adjuvant chemoradiotherapy with cisplatin (40 mg/m^2^). However, cisplatin has side effects such as hematological implications (anemia, neutropenia, and thrombocytopenia), gastrointestinal disorders (nausea, vomiting, diarrhea, constipation), and fatigue. *Zingiber officinale* contains bioactive compounds that act on pregnancy and postoperative nausea, chemotherapy-induced nausea and vomiting, and also in the management of fatigue, myalgia, and insomnia. This study aimed to evaluate the effects of ginger on chemotherapy-induced nausea and vomiting in patients with cervical cancer undergoing treatment with cisplatin and radiotherapy.

**Methods and analyses::**

A randomized intervention clinical and controlled trial with a triple-blind design is described, comparing the effects of institutional antiemetic therapy alone, as well as in combination with 2 different ginger concentrations.

**Ethics and dissemination::**

Due to the nature of the study, we obtained approval from the Division Ethics Committee of Liga Contra o Câncer. All participants signed an informed consent form prior to randomization. The results of this study will be published in peer-reviewed journals. The data collected will also be available in a public repository of data.

**Trial registration number::**

This study is registered in the Brazilian Registry of Clinical Trials under number RBR-47yx6p9. This study was approved by the Division Ethics Committee of Liga Contra o Câncer under CAAE 40602320.0.0000.5293.

STRENGTHS AND LIMITATIONS OF THIS STUDYThis is the first randomized controlled trial comparing ginger doses with placebo doses for controlling chemotherapy-induced nausea and vomiting (CINV).Inclusion criteria allow for homogeneity of subjects and less risk of bias.Blinding of assessors and standardization of protocols enhance this trial's internal validity.The primary outcome includes controlling nausea and vomiting or common terminology criteria for adverse events (CTCAE) (gastrointestinal disorders - nausea/vomiting).

## Introduction

1

Cancer is a leading cause of morbidity and mortality worldwide, with 19.2 million new cases reported annually.^[1]^ In 2020, an estimated 9.9 million deaths occurred due to cancer, and the estimated prevalence over the past 5 years involved 50.1 million people. Among the malignant neoplasms, cervical cancer predominantly affects females. It is the fourth most frequent cancer worldwide with a prevalence of 1.5 million cases, and an incidence of 605,000 new cases worldwide.^[1]^ The cervix tumor has an invasive feature with the capacity to proliferate to surrounding organs such as the vagina, bladder, and rectum, as well as dissemination and involvement of structures distant from its place of origin.^[1,2]^ This neoplasm is mainly caused by human papillomavirus (HPV) infection, early sexual activity with multiple partners, smoking, and prolonged use of oral contraceptives.^[3]^

The treatment of cervical cancer has 3 aspects: surgery, chemotherapy, and radiotherapy, which can be performed alone or in combination. According to the International Federation of Gynecology and Obstetrics staging system, patients with stages IB I, IB I microscopic (small dimension <4 cm), are indicated for radiotherapy (RDT) or adjuvant chemoradiotherapy with cisplatin (40 mg/m^2^). Administration of weekly cisplatin with radiotherapy shows superior results compared to isolated radiotherapy, and promotes less toxicity than in conjunction with other drugs.^[4]^ However, cisplatin has side effects, such as hematological abnormalities (anemia, neutropenia, and thrombocytopenia), gastrointestinal disorders (nausea, vomiting, diarrhea, constipation), and fatigue.^[1,5,6]^

Chemotherapy-Induced Nausea and Vomiting (CINV) are considered severe side effects that most commonly occur during cancer treatment, including treatment with cisplatin.^[7–9]^ The management of these side effects becomes difficult to control owing to the multiple central and peripheral neural stimuli caused by the drugs.^[4,10,11]^

Repetitive episodes of nausea and/or emesis may result in decreased food intake causing loss of nutrients and water, metabolic disorders due to gastric losses, anorexia, fatigue, and increased risk of acute renal failure. In addition, psychosocial aspects such mental deterioration and acceptance of body self-image can compromise treatment adherence and cause abandonment.^[7,12]^

As *Zingiber officinale* contains bioactive compounds, such as gingerols, shogaols, zingiberene, zingerone and paradol (gingerol and shogaol) it is affective against pregnancy and postoperative nausea such as CINV, as well as in the management of fatigue, myalgia, and insomnia.^[13–17]^ However, these active components directly influence the antral motility, optimizing gastric emptying and intestinal peristalsis. They also affect the central nervous system, thus modulating serotoninergic pathways of 5-HT^3^ receptors, as well as the drugs mentioned above.^[16]^ Experimental studies confirm the safety of the root and its effectiveness in the treatment and prevention of secondary symptoms of chemotherapy.^[18,19]^

Therefore, this study aims to evaluate the effects of ginger on CINV in patients with cervical cancer undergoing treatment with cisplatin and radiotherapy.

### Objectives

1.1

To evaluate the effects of ginger on CINV in patients with cervical cancer treated with cisplatin and radiotherapy.

## Methods and analysis

2

Our protocol adheres to the Standard Protocol Items for Randomized Trials (SPIRIT) and Consolidated Standards of Reporting Trials (CONSORT) statements.^[20]^

### Trial design

2.1

This is a protocol of a randomized clinical and controlled intervention trial with a triple-blind design, which compares the effects of institutional antiemetic therapy alone as well as with the use of 2 different ginger concentrations.

### Population

2.2

The treatments will be carried out in a reference center for cancer care in Brazil. Recruitment of participants is ongoing at a referral center for cancer treatment. After reading and signing the informed consent form, patients who meet the eligibility criteria will be included in the research.

### Eligibility criteria and recruitment

2.3

The study will include patients over 18 years of age, who were diagnosed with cancer of the uterine cervix on histological confirmation. Furthermore, they were indicated for treatment with cisplatin 40 mg/m^2^ associated with radiotherapy and had capsule swallowing capacity. Figure 1 shows the study flow.

**Figure 1 F1:**
[figure not shown]
CONSORT 2010 flow diagram.

### Interventions

2.4

The control group will swallow capsules containing 500 mg of placebo (77.80% pharmaceutical starch + 10.10% pharmaceutical talc + 10.10% microcrystalline cellulose + 1% magnesium stearate + magnesium dioxide 1% colloidal silicon, contained in white/blue gelatin capsules of size No. 00). Placebo capsules will be swallowed with approximately 250 ml of water every 12 hours, totaling to 1 g per day.

Experimental group 1 will be composed of patients who will receive capsules containing 250 mg of the ginger extract contained in white/blue gelatin capsules No. 00. The capsules will be swallowed with approximately 250 ml of water every 12 hours, totaling to 500 mg per day. The ginger used will be dehydrated and crushed into a powder form without any chemical additives.

Finally, experimental group 2 will receive capsules containing 500 mg of the ginger extract contained in white/blue gelatin capsules No. 00 and will be swallowed with an average of 250 ml of water every 12 hours totaling to 1 g per day. The ginger will be dehydrated and crushed into a powder form without any chemical additives.

### Questionnaire

2.5

In the first query, the participants will answer a standardized questionnaire with information on demographic characteristics, including age, marital status, profession, schooling, socioeconomic classification, and risk factors (alcoholism, smoking, HPV, use of oral contraceptives, and whether Pap test was regularly performed).

### Outcomes

2.6

#### Primary outcome

2.6.1

Seven relevant time points will be considered for evaluating the results based on the chemotherapy protocol of cisplatin with radiotherapy: baseline (P0), 7 days after the first dose of medication (P1), on every consecutive 7th day during a break in treatment (P2, P3, P4, P5, and P6), and 15 days after the last dose (P7).

The primary outcome includes controlling nausea and vomiting as evaluated using the Common Terminology Criteria for Adverse Events or CTCAE (gastrointestinal disorders-nausea/vomiting).^[21]^ The CTCAE for nausea (a disorder characterized by a queasy sensation and/or the urge to vomit) will be classified as Grade 1 (loss of appetite without alteration in eating habits), Grade 2 (oral intake decreased without significant weight loss, dehydration, or malnutrition), or Grade 3 (inadequate oral caloric or fluid intake; tube feeding, parenteral nutrition, or hospitalization indicated). Vomiting (a disorder characterized by the reflexive act of ejecting the stomach contents through the mouth) will be classified as Grade 1 (intervention not indicated), Grade 2 (outpatient IV hydration: medical intervention indicated), Grade 3 (tube feeding, parenteral nutrition, or hospitalization indicated), Grade 4 (life-threatening consequences), or Grade 5 (death) (Table 1).

**Table 1 T1:** Outcome measurements.

Outcome measurement	Explanation	Time points for assessment
CTCAE	Common terminology criteria for adverse events	T1, T2, T3, T4, T5, and T6
EORTC QLQ C30	European Organization for Research and Treatment of Cancer Quality of Life Questionnaire Core 30	T1, T2, T3, T4, T5, and T6
EORTC QLQ Cx24	EORTC quality of life cervical cancer module	T1, T2, T3, T4, T5, and T6
MGT	Morisky-Green Test to evaluate medication adherence	T1, T2, T3, T4, T5, and T6

#### Secondary outcome

2.6.2

Secondary outcomes will be quality of life module of the European Organization for Research and Treatment of Cancer and Cervical Cancer- Specific Quality of Life Questionnaire, and medication adherence as evaluated using the Morisky-Green Test.^[22–25]^

The European Organization for Research and Treatment of Cancer is an internationally validated and widely used cancer-specific health related quality of life (HRQoL) instrument. It contains 5 scales of functioning (physical, social, role, cognitive, and emotional functioning), 8 symptom scales (fatigue, nausea/vomiting, pain, dyspnea, sleep disturbances, appetite loss, constipation, and diarrhea), and evaluations of financial impact and overall quality of life. Raw scores are linearly converted to a scaled score in a range between 0 and 100.^[22]^ For the functioning scales and global QOL, higher scores indicate better functioning; for the symptom scales, higher scores indicate higher symptom burden. Furthermore, the cervical cancer-specific EORTC QLQ-CX24 consists of 5 multi-item scales on clinically distinct dimensions (sexual functioning, body image, gastrointestinal, urologic, and vaginal symptoms) and several single-item measures.^[23]^

To evaluate medication adherence, we will use the version of the Morisky-Green Test which includes the following questions: Do you sometimes have difficulty remembering to take your medication? Do you sometimes not pay attention to taking your medication? When you feel better, do you sometimes stop taking your medication? Sometimes, if you feel worse after taking medication, do you stop taking it?^[24]^

The evaluation of the results is described in Table 2. All possible adverse effects will be recorded and qualified during the treatment period using questionnaires developed for this protocol. Any adverse events will be reported and discussed in the Results section of the manuscript. Any breach of confidentiality, study protocol, or adverse events attributable to this study will be reported to the research ethics committees.

**Table 2 T2:** Schedule of enrollment, interventions, assessments and data collection.

Study period								
	Enrollment/baseline	Intervention						Follow-up
Time point	T0	T1	T2	T3	T4	T5	T6	15 d
Enrollment	X							
Eligibility screen	X							
Informed consent	X							
Randomization	X							
Interventions								
Ginger capsules 250 mg		X	X	X	X	X	X	
Ginger capsules 250 mg		X	X	X	X	X	X	
Placebo		X	X	X	X	X	X	
Assessments								
General condition								X

### Screening

2.7

After a nursing consultation, the elected patient will fill a registration form containing patient identification data and clinical and demographic information. Next, a pharmacist will dispense a bottle of capsules corresponding to the participant's previously determined group allocation.

### Follow-up

2.8

Follow-up data including a general condition assessment will be recorded during the follow-up period corresponding to the multiple time points. The details are presented in Table 2.

Each patient will remain in the study for 7 weeks or until the end of chemotherapy treatment if the chemotherapy period is scheduled to end before the 7-week intervention. Recruitment and data collection will take place at the following times:

**Period 1:** Recruitment (Day 0) at the time of chemotherapy initiation.**Period 2:** Intervention (Weeks 16), data will be recorded every 7 days or at the time of each new weekly chemotherapy dose.**Period 3:** Time after intervention (at least 7 but within 15 days after completion of treatment), follow-up for long-term results.The last meeting between the researcher and patient can take place via phone call or in-person, as it will be at least 1 week after the last infusion of the antineoplastic therapy.At the weekly chemotherapy session, the principal researcher will check the number of remaining capsules to assess the adherence to study protocol. In all, will be 7 in-person possibilities for data collection. If no return is established, telephone contact will be attempted in the last week.

### Sample size

2.9

The sample size calculation will be established using G Power Software version 3.1.9.2 (https://www.psychologie.hhu.de/arbeitsgruppen/allgemeine-psychologie-und-arbeitspsychologie/gpower), considering a Cohen effect size of 0.40, a test power of 0.80, and a significance level of 5% (*P* value <.05).^[26]^ The sample is estimated to be of 39 patients with a potential addition of 20%, totaling 48 participants, which will be equally allocated (1:1:1) into 3 groups of 16 patients each (the ginger capsules 250 mg group, ginger capsules 500 gm group, and placebo group).

### Randomization and allocation concealment

2.10

On providing informed consent, eligible participants will be randomized by the Software Research Randomizer program using block design (1:1:1; experimental group 1, experimental group 2, or control group). Patients will be randomized into 3 intervention groups.

To ensure blind allocation, an off-site randomization schedule will be followed. This schedule will be prepared by a researcher at the Institute of Education, Research and Innovation (Liga Contra o Câncer), who will have no contact with any participants throughout the trial and will not be involved in the recruitment, screening, assessment, enrollment, or treatment process. To enroll a participant, the primary researcher will email the consenting participant's name to the researcher at the LIGA. These details will be entered into the allocation spreadsheet, and the corresponding treatment allocation and participant identification number will be emailed to the researcher.

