### Blinding

2.11

Research participants, group researchers, and individuals who assess the outcomes will not have access to the details of group assignments. This ensures that bias for or against the tested treatment is unlikely to occur.

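### As written, the randomisation email sends the treatment allocation back to a researcher whom the blinding section says must not have it

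*Protocol article*

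**What the plan says.** All references are to the protocol article.

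- **Randomization and allocation concealment (2.10).** The schedule is prepared off site by a researcher "who will have no contact with any participants throughout the trial and will not be involved in the recruitment, screening, assessment, enrollment, or treatment process". When a patient is to be enrolled, "the primary researcher will email the consenting participant's name to the researcher at the LIGA". The details go into an allocation spreadsheet, and "the corresponding treatment allocation and participant identification number will be emailed to the researcher". Allocation is blocked 1:1:1; no block size is given.
- **Blinding (2.11).** "Research participants, group researchers, and individuals who assess the outcomes will not have access to the details of group assignments".
- **Screening (2.7).** After the nursing consultation, "a pharmacist will dispense a bottle of capsules corresponding to" the group already assigned to that patient. No bottle or kit code is mentioned.
- **Follow-up (2.8).** "At the weekly chemotherapy session, the principal researcher will check the number of remaining capsules to assess the adherence to study protocol". Also: "The last meeting between the researcher and patient can take place via phone call or in-person".
- **Data management (2.12).** One trained team member collects the data. The article does not say whether this is the enrolling researcher.
- **Abstract, Trial design (2.1) and Discussion.** Each calls the trial triple-blind, and the strengths list adds that assessors are blinded.

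**The concern.** The article describes a flow of information that discloses what the next section says is withheld. This is a stated procedure in conflict with a stated rule, so it is more than a detail left to a fuller document. Two separate protections are affected.

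**Blinding.** The primary outcome is the CTCAE grade for nausea and vomiting. The nausea grades turn on appetite and oral intake, which are partly a matter of report and judgement. If someone who knows the arm does the grading or influences it, the ginger-placebo contrast could shift.

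**Concealment.** In a blocked list, knowing past assignments gives information about the next one. An enroller with that knowledge could, even unintentionally, affect which patient is entered next. This route does not depend on who grades the outcome.

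With 16 patients per arm, a few affected enrolments or grades could matter, and no later analysis restores lost blinding.

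**Working it through.** The article gives no figure to reproduce. The main check sets the sections side by side.

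**1. Who receives the email?** Section 2.10 mentions two people: the off-site schedule holder and the primary researcher who makes the request. The schedule holder already has the spreadsheet and would not email the allocation to themselves. The enrolling primary researcher is therefore the natural recipient, though the sentence does not name the role.

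**2. What is in the email?** Two items are listed, the treatment allocation and the participant identification number, so the allocation is not simply the number. The only allocations that 2.10 names are the two experimental groups and the control group. No code is described there or in 2.7.

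**3. Does this conflict with 2.11?** Yes. That section covers the group's researchers as well as the outcome assessors, and the primary researcher is one of the former. The conflict stands whether or not this person assesses outcomes.

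**4. Does the recipient meet patients?** This holds only if the primary researcher of 2.10 is the principal researcher of 2.8. In that case the person counts capsules with each patient every week. The article assigns no other weekly task to that role.

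**5. Does the recipient need the allocation?** On the text, no. A pharmacist dispenses.

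**6. How far could later allocations be predicted?** The input from Sample size (2.9) is 48 patients, 16 per arm. Three assumptions are needed: the emailed allocations are uncoded, the enroller knows the block size and boundaries, and the block size is as shown.

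- *Blocks of 3.* There are 48 / 3 = 16 blocks. In each block the first allocation is a 1-in-3 guess, the second 1 in 2, and the third certain. So 16 of 48 allocations are known beforehand. The expected number of correct guesses is 16 × (1/3 + 1/2 + 1) = 16 × 11/6 = 29.3 of 48, against 48 × 1/3 = 16 with no information.
- *Blocks of 6.* There are 48 / 6 = 8 blocks. The sixth allocation in each is always certain, so at least 8 of 48 are known beforehand.

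These figures illustrate the range. They do not describe the actual trial, whose block size is not given.

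**The case against.** The strongest defence is that the emailed allocation may be a code. The paragraph in 2.10 opens with the aim of keeping allocation blind, 2.11 states the rule plainly, and Interventions (2.4) gives all three arms white/blue No. 00 capsules. A coded allocation would reconcile the sections, and bottle coding is the kind of detail a condensed article often leaves out. This stands in part: it means the trial may be properly blinded in practice. It does not rescue the text, which says that the treatment allocation is sent and gives no sign that it is masked.

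A reader might go further and infer that the person who receives the allocation runs the weekly visits and collects the primary outcome, so that the trial is simply not triple-blind. The article does not support this. Section 2.8 gives the principal researcher the weekly capsule count and no other weekly task. Section 2.12 assigns data collection to a trained team member who may be someone else. No section says who grades CTCAE, and 2.11 lists outcome assessors separately and states that they are blind.

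The prediction argument is also conditional, as the working shows. The schedule is held off site by someone without patient contact, and each allocation is requested only after consent. Those safeguards protect the list itself. They do not stop an enroller from accumulating past allocations if these arrive uncoded.

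**Conclusion.** The point holds as an internal contradiction: as written, 2.10 discloses the allocation to a member of the research team, against 2.11 and the triple-blind label. It should be corrected, and promptly, because Population (2.2) says recruitment is ongoing.

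The size is up to all 48 allocations if they are sent uncoded. Predictability of later allocations runs from at least 8 of 48 certain (blocks of 6) to 16 of 48 certain (blocks of 3), on the assumptions given above.

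The core conclusion rests on one reading, that the unnamed recipient is the enrolling primary researcher. Weekly patient contact rests on a second, that primary and principal researcher are the same role. Biased grading of the primary outcome would need a third link that the article does not supply, so it is a possibility and not a finding.

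**What to change.** 1. In 2.10, state that the off-site researcher sends the allocation only to the dispensing pharmacist, or sends it only as a coded bottle number that does not reveal the arm.
2. State that the enrolling researcher receives just the participant identification number and confirmation of enrolment.
3. Reconcile 2.7, 2.8, 2.10 and 2.11, so that each role that handles the allocation or meets patients is named consistently and its access to the allocation is clear.
4. If uncoded allocations have already gone to the enrolling researcher, stop this, report it, and do not describe those patients as enrolled and assessed under triple-blinding.

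The cost is small. If practice is already coded, a sentence in 2.10 and matching wording elsewhere suffice. If not, the email must be rerouted or the bottles coded. The pharmacist already dispenses, so rerouting needs no new role.
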